**Methods:**

A permuted block randomized (1:1 allocation) intervention trial will be conducted involving young, physically-active men and women. A target sample size of 32 will be recruited and enrolled participants will undergo baseline testing involving extended-field-of-view ultrasound imaging and shear wave elastography of the biceps femoris long head muscle, maximal hamstrings strength testing in both the RDL and NHE, and on-field sprint performance and biomechanics. Participants will complete the 6-week training intervention using either the RDL or NHE, according to group allocation. Baseline testing will be repeated at the end of the 6-week intervention followed by 2 weeks of detraining and a final testing session. The primary outcome will be regional changes in fascicle length with secondary outcomes including pennation angle, muscle cross sectional area, hamstring strength, and maximal sprint performance and biomechanics. An exploratory aim will determine changes in shear wave velocity.

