**Fig. 1 Fig1:**
[figure not shown]
Proposed experimental design and outcome measures at each testing time-point

An *a priori* power calculation using R statistical software and “WebPower” package (wp.kanova function) [57] was performed. Using an effect size based the median Cohen’s d extracted from several relevant studies investigating the effects of NHE on the primary aim of fascicle length changes [19, 21, 26, 54, 58] and converting to Cohen’s f (f = 0.8), 2 experimental groups (RDL vs. NHE), a total of 12 factors (levels of intervention x time x imaging location (proximal, mid-belly, distal) = 2 × 2 × 3), α = 0.05, and power = 0.80, a total sample size of 11 participants per group will be required. This sample size is consistent with previous investigations of fascicle length following NHE training [19, 21, 26, 54, 58]. Using a conservative effect size (Cohen’s d = 0.5) based on observed 2% differences detected in sprint times between two eccentric training interventions (Cohen’s d = 0.87) [47] and converting to Cohen’s f (f = 0.25), a total sample size of 28 (N = 14 per group) will be required for the secondary aims. Based on the larger sample size and accounting for a 10% attrition rate, a total of 16 participants per group (N = 32 in total) will be recruited from the University of Wisconsin to participate. Participants will be compensated on a pro-rated basis for completing study visits and provided their strength and sprint results.

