Participants will be allocated to either the RDL or NHE training group using a random permuted block randomization (1:1 training group allocation) using *a priori* computer-generated group numbers. Each participant will undergo the 6-week intervention program based upon their group allocation (see *Intervention*). A 6-week period was chosen due to previous observations that additional changes in fascicle length (primary outcome) were minimal with NHE training lasting > 6 weeks [47, 59] and is consistent with previous investigations of architectural changes induced by NHE [54, 58]. Following the 6-week intervention, participants will return to the lab for post-intervention assessments of regional ultrasound of the hamstrings, RDL and NHE strength testing, and sprint testing, which will be carried out in the same manner as baseline assessments. Fascicle length changes are known to return to baseline values within 2 weeks after the cessation of NHE [54, 60]. To investigate the potential short-term washout effects of the training intervention on the primary and secondary outcomes, participants will be asked to return to the lab following a 2-week detraining period. During these 2 weeks, participants will be encouraged to resume all normal activities but limit any outside eccentric hamstring strength training.

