### Outcome measures & statistical analysis

All outcome results will be included in an anonymous database for statistical analysis. Using an intention-to-treat analysis, separate linear mixed effects models will be used to compare the effect of RDL and NHE on the primary outcome of biceps femoris long head fascicle length. Similar analyses will be performed for secondary analyses related to pennation angle, anatomical cross-sectional area, muscle thickness, and SWS. Full factorial models will be implemented with fixed effects of intervention group, muscle region, and time and a random effect to account for between-participant variation. Effect sizes will be calculated.

Sprint performance outcomes will be summarized using descriptive statistics. Given that the expected changes in sprint performance are numerically small but may still represent meaningful changes in overall sport performance and improvement, we will set *a priori* thresholds to describe the magnitude of change. Small, medium and large improvements in sprint times will be defined as < 2%, 2–4%, and > 4%, respectively, based off changes in 40 m sprint times observed previously [47, 82].

Discrete kinematic variables will be summarized using descriptive statistics and compared between time points for the maximal sprint using linear mixed effects models [83]. Due to the continuous time series data extracted from the IMUs, statistical parametric mapping (SPM) will also be used to determine any within-participant changes in kinematics throughout the entire sprint. SPM allows for the analysis of the entire time series and has been used in a variety of biomechanical studies [84–86]. Specifically, within-subject differences in trunk, hip, knee, and ankle kinematics will be calculated between test sessions

As an additional description of sprint performance, we will characterize the horizontal force production as detailed by Samozino et al. and adapted by others [1, 47, 87]. Descriptions of the theoretical maximal horizontal force (F_0_), velocity (v_0_), and maximal power output (P_max_) will be derived from participants’ split times and each participant’s body mass according to previous works [44, 88]. Intervention assessments for each variable across each time point will be compared using linear mixed effects models and R software [89, 90]

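### A mixed-sex trial with 16 per arm states neither a sex stratum nor a sex term in its model; adding both would be a cheap gain in precision for absolute-unit secondary outcomes

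*Protocol article*

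**What the plan says.** The Abstract describes a trial "involving young, physically-active men and women", and the inclusion criteria under Overall study design contain a condition that applies to women. The share of each sex is not given. On size, the same section says "a total of 16 participants per group (N = 32 in total) will be recruited".

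Allocation is described after Fig. 1 in that section: "Participants will be allocated to either the RDL or NHE training group using a random permuted block randomization (1:1 training group allocation"), from computer-generated numbers. No stratification factor and no block size are named.

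Under Outcome measures & statistical analysis, the mixed model for fascicle length has "fixed effects of intervention group, muscle region, and time and a random effect to account for between-participant variation". The article extends this model: "Similar analyses will be performed for secondary analyses related to pennation angle, anatomical cross-sectional area, muscle thickness, and SWS". For F0, v0 and Pmax it specifies linear mixed effects models across time points without listing their terms. It sets out no specific model for RDL or NHE strength.

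**The concern.** In a mixed model with a participant random effect, a constant difference between men and women drops out of the comparison of changes. A difference in how much they change does not. If it is not modelled, it stays in the residual and widens the interval. If the arms also differ in sex mix, it moves the estimated arm difference in that particular trial.

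This is plausible for outcomes in absolute units. RDL test loads rise in percentage steps, RDL training intensity is expressed relative to each participant's 3RM, and the sprint force and power values are derived using body mass. If two people gain the same percentage, the stronger or heavier one gains more in kg, N or W. How far men and women would differ on this account is not stated and has to be assumed.

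At stake is precision on the secondary outcomes. There is also an avoidable analytic choice: if the arms come out clearly uneven, adjusting for sex only after seeing that is a data-driven decision.

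**Working it through.** **The plan's own figure.** The article gives no figure for sex balance. Its total reproduces: 28 required for the secondary aims, 28 / 0.9 = 31.1, rounded up to 32, or 16 per arm.

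**Step 1. Chance of a sex imbalance between arms.** Inputs: N = 32, 16 per arm, and W women (not stated; three values tried). Without stratification, the number of women in one arm is hypergeometric, provided sex is unrelated to entry order:

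P(X = x) = C(W, x) · C(32 − W, 16 − x) / C(32, 16)

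For W = 16, C(32, 16) = 601,080,390.
- P(X = 8) = 12,870² / 601,080,390 = 0.2756
- P(X = 7 or 9) = 2 × 11,440² / 601,080,390 = 0.4355
- P(X = 6 or 10) = 2 × 8,008² / 601,080,390 = 0.2134
- P(10:6 or worse) = 1 − 0.2756 − 0.4355 = 0.289
- P(11:5 or worse) = 0.289 − 0.2134 = 0.076

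| Women of 32 | Differ by ≥ 2 | Differ by ≥ 4 | Differ by ≥ 6 |
|---|---|---|---|
| 16 | 0.724 | 0.289 | 0.076 |
| 12 | 0.716 | 0.273 | 0.066 |
| 8 | 0.685 | 0.220 | 0.037 |

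Simulated permuted blocks of 2, 4 and 8 gave 0.288 to 0.289 for a difference of 4 or more with 16 women, so block size does not alter this.

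**Step 2. Shift in the arm difference.** Let D be the sex difference in mean change, in within-sex SDs of the change (assumed). The shift is D × (difference in number of women / 16).
- 10:6 split: 4/16 = 0.25, so 0.25 × D, which is 0.125 SD at D = 0.5 and 0.25 SD at D = 1.0.
- 11:5 split: 6/16 = 0.375, so 0.375 × D.

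For scale, the standard error of the arm difference in the same units is √(2/16) = 0.354 SD.

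**Step 3. Precision even with perfect balance.** If sex is left out, the variance of the change is multiplied by 1 + p(1 − p)D², where p is the share of women. With p = 0.5 this is 1 + D²/4. The equivalent number of participants lost is 32 × (1 − 1/factor).

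| D (assumed) | Variance factor | SE increase | Participants lost, of 32 |
|---|---|---|---|
| 0.25 | 1.016 | 0.8% | 0.5 |
| 0.5 | 1.0625 | 3.1% | 1.9 |
| 0.8 | 1.16 | 7.7% | 4.4 |
| 1.0 | 1.25 | 11.8% | 6.4 |

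With 8 women of 32, p(1 − p) = 0.1875 and the cost is smaller: at D = 1.0 the factor is 1.1875 and the SE rises by 9%.

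**Step 4. What this means for power, as an illustration.** Take 14 per group and a true difference of 1 within-sex SD (assumed), normal approximation. Adjusted: Φ(√7 − 1.96) = Φ(0.686) = 75.4%. Unadjusted: Φ(√7/√factor − 1.96), which is 74.7%, 72.8%, 69.0% and 65.8% for D = 0.25, 0.5, 0.8 and 1.0.

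**The case against.** The case against is strong in several places.

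- **The article is condensed.** It does not say that there is one list for both sexes, and the full protocol may stratify. That stands: a reader might infer a single unstratified list, but the text supports only that no stratum is named.
- **The listed terms belong to the ultrasound outcomes.** For F0, v0 and Pmax no terms are listed, and for strength no model is set out. A reader might conclude that sex has been excluded from those analyses; the article does not say so. Of the absolute-unit outcomes named here, only muscle area falls clearly under the stated model.
- **A clear imbalance is not likely.** A 9:7 or worse split is (about 0.7), but it matters little. A 10:6 or worse split has roughly a one-in-four chance.
- **Chance imbalance is not bias.** A reader might call this confounding. Randomisation keeps the comparison valid, and the interval already allows for chance differences in sex mix. The shift in Step 2 is conditional on the split that happens to occur.
- **The sex difference in change has no source in the document.** This stands, and at D = 0.25 the issue all but disappears.
- **The primary outcome and the sample size are not shown to suffer.** No argument here reaches regional fascicle length. The planning effect sizes are standardised and come from fascicle length and sprint times, so they do not show that the trial is underpowered on this account. Sprint-time improvement is graded in per cent, so the absolute-unit argument does not reach it.

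What survives is that the article describes its allocation method and writes out a model, that sex is in neither, and that a better choice costs little.

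**Conclusion.** The point holds as an inexpensive improvement in design and analysis, not as an error. The article names sex neither as a stratum nor as a term in its stated model, although it enrols both sexes with 16 per arm. The chance of a 10:6 or worse split is 0.22 to 0.29 for 8 to 16 women of 32, assuming no stratification and that sex is unrelated to entry order.

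The cost depends on the assumed sex difference in change: an SE increase of about 3% or less up to 0.5 SD, and about 8 to 12% at 0.8 to 1.0 SD with equal numbers of each sex. It concerns mainly muscle area, F0, Pmax and RDL and NHE strength.

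**What to change.** 1. In Overall study design, state that the permuted blocks are formed separately for men and women, with small blocks. If the full protocol already does this, one sentence settles the matter.
2. In Outcome measures & statistical analysis, prespecify sex and sex × time as fixed effects in the between-arm models for the absolute-unit outcomes: muscle area, F0, Pmax, RDL strength and NHE strength. Stratifying evens out the sex mix, but the model terms are what take the sex-related spread out of the residual.
3. If enrolment has begun, leave the allocation alone and make only the model change, before any comparison by arm is seen.

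The cost is one more computer-generated list and a few degrees of freedom: with three test sessions, one coefficient for sex and two for sex × time. Stratifying can also leave the arms slightly unequal. With blocks of 4, an unfinished block leaves a difference of at most 2 within each sex, so at worst 18:14 overall.

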### Ultrasound

Participants will lay prone on an exam table with their hips and knees in a neutral position and feet off the end of the exam table. Participants will lie quietly at rest for 3 min prior to image acquisition to normalized fluid shift within the muscle [61, 62].

Ultrasound B-mode images will be collected unilaterally from the biceps femoris muscle of the dominant limb for each participant using a Logiq P9 ultrasound system (GE Healthcare, Waukesha, WI) and a linear array transducer (L3-12-RS, 47.1 mm aperture). The same researcher ([name]) will perform all image acquisitions and will be blinded to participant group allocation. The thigh length from the ischial tuberosity to the midpoint between the femoral condyles will be measured and recorded. Skin marks will be made at 33%, 50%, and 67% of the thigh length from the ischial tuberosity to standardize imaging locations between participants and correspond to approximately proximal, mid-belly, and distal regions of the hamstring muscle, respectively [63, 64].

Three longitudinal extended-field-of-view images of the entire biceps femoris muscle (i.e., from the most proximal to the most distal visualization of the muscle-tendon junctions) will be collected. According to extended-field-of-view image acquisition recommendations and previous studies [65–71], preliminary scans will be performed to determine the proximal and distal muscle-tendon junctions A longitudinal image will be captured along the path of the fascicle plane spanning the entire length of the biceps femoris muscle (Fig. 2).

**Fig. 2 Fig2:**
[figure not shown]
Representative longitudinal extended-field-of-view image of the biceps femoris long head muscle with representative fascicles in the proximal, mid-belly, and distal regions (from left to right) outlined and highlighted in yellow

Three transverse extended-field-of-view images will be captured at the proximal, mid-belly, and distal locations to determine regional anatomical cross-sectional area of the biceps femoris long head muscle. The transducer will be placed perpendicular to the skin and the entire cross-sectional view of the hamstrings muscles imaged (Fig. 3) [70, 72]. A transverse image using traditional field-of-view B-mode imaging will also be captured at these locations.

**Fig. 3 Fig3:**
[figure not shown]
Representative transverse extended-field-of-view image of the biceps femoris long head muscle (BFlh), semitendinosus (ST), and semimembranosus (SM) muscles. Anatomical cross-sectional area will be calculated from the transverse ultrasound images

To determine changes in tissue stiffness characterized by ultrasound SWS for the exploratory aim, the same transducer will be placed in the same proximal, mid-belly, and distal locations in a longitudinal view. A traditional field-of-view B-mode image will also be captured at these locations. This orientation (parallel to the muscle fascicles) has been shown to be more reliable for measuring SWS than transverse views [73, 74]. Minimal pressure will be applied to the muscle and the shear wave box (for wave speed detection) will be placed in the middle of the imaged muscle region (Fig. 4). Shear wave maps will be generated by the ultrasound system and SWS measures will be extracted from the middle of the SWS map using the measurement tools of the ultrasound system.

**Fig. 4 Fig4:**
[figure not shown]
Representative ultrasound (A) B-mode image of the mid-belly biceps femoris long head muscle, (B) shear wave map at the same location, and (C) Q-box measures within the shear wave map with corresponding values in bottom lefthand subpanel

### Nordic hamstring exercise and romanian deadlift strength testing

Hamstrings strength testing will be determined for 3 repetitions of the NHE and three-repetition maximum (3RM) in the RDL following ultrasound imaging. Prior to each test, participants will perform a standardized 5-minute general warm-up on a stationary bike followed by a task-specific warm-up including 3 sets of submaximal trials of the NHE and RDL (Additional File 1, Table A1). The RDL testing will precede the NHE for all participants with a full 15-minute rest between exercises to minimize fatigue.

The RDL will be performed in a multi-purpose, commercial power rack with a standard 20 kg Olympic barbell. Incremental load increases (5–20%) will be added for each subsequent trial until the participant cannot complete 3 repetitions through the full range of motion using proper technique. Participants will use wrist straps during the 3RM determination so maximal RDL loads will not be influenced by the participant’s grip strength. A 3 min rest will be administered between all warm-up and testing sets to allow for full recovery.

The NHE will be performed on the Nordbord (Vald Performance, Queensland, Australia), which is a reliable device to assess maximum eccentric knee flexor strength [75]. NHE testing will be performed consistent with previous investigations [2, 47, 54, 59, 60]. Participants will begin kneeled on the device in approximately 90° of flexion while their ankles are secured into fixed hooks placed superior to the lateral malleoli and oriented vertically. Participants will be asked to maintain a dorsiflexed ankle when performing the NHE [76]. Participants will cross their arms over their chest and be instructed to maintain a neutral (0° extension) hip posture while lowering their upper body to the ground as slowly as possible. They will be instructed to uncross their arms and gently catch themselves before hitting the ground if they feel their hips alignment “break” (i.e., they are unable to maintain 0° hip alignment).

Following submaximal NHE practice trials, participants will begin the maximal test, which will consist of 1 set of 3 maximal repetitions. Minimal rest (< 2 s) will be permitted between reps. If participants can control the eccentric portion of the movement towards full knee extension (i.e., not falling beyond ~ 20° knee flexion), then participants will repeat a subsequent set of 3 maximal repetitions while holding external load (5 kg increment) positioned on sternum. In the event participants need to sequentially add external load for maximum NHE testing, full recovery (3 min) will be administered between sets.

### Maximum sprint testing data collection

A minimum of 15 min between strength testing and sprints will be administered. Sprints will be performed on artificial turf to minimize any effects of weather and variations in ground surface conditions on sprint performance outcomes. Prior to sprinting, participants will be weighed for subsequent sprint kinetics analysis (see *Outcome Measures & Statistical Analysis*) and to determine an accurate mass for proper calibration of the IMU system.

Participants will go through a standardized warm-up (Additional File, Table A2) [2, 77]. Following the warm-up, the participants will rest for 5 min to allow for placement of eight IMUs (Xsens MVN, Xsens Technologies B.V., The Netherlands) on the sternum, sacrum, and bilaterally on the thighs, legs, and foot. This system is reliable and validated to measure joint kinematics during dynamic trials and related to sprint mechanics [78–80]. Once the system is successfully calibrated, participants will then perform three maximal 60 m sprints.

Timing gates (SmartSpeed, Vald Performance, Queensland, Australia) will be placed at the start line (0 m), 5, 10, 20, 30, 40, 50, and 60 m. Each participant will perform a total of 3 maximal 60 m sprints from a standing position with 90 s rest in between each trial to minimize the effects of fatigue. Participants will begin with their front foot 0.5 m behind the first timing gate to prevent premature activation of the timing gates.

### Intervention

All training sessions will be supervised by key study personnel with more than 4 years of exercise testing and prescription to monitor the training sessions and to keep the assessor for the primary outcome (i.e., fascicle length) blinded to the group allocation of individual participants. The key study personnel responsible for implementing the training intervention will contact each participant weekly for training sessions. A metronome (60 Hz) will be used to provide feedback for the execution of the eccentric contraction time throughout the range of motion.

Prior to each training session, participants will undergo a standardized warm-up that will include a 5 min general warm-up on a stationary bike followed by specific dynamic drills to prepare the athlete for the training session (Additional File, Table A1). The training intervention groups will undergo the same program with the only difference being the interventional hamstring exercise. The program will consist of a 2-week familiarization period followed by 4-weeks of progressive training [54]. A sample of the overall resistance training program is shown in Table 1 with each training session expected to last 45–60 min.

**Table 1 Tab1:** Overview of the entire 6-week resistance training program

*Exercise*	*Sets x Repetitions (ECC:ISO:CON tempo)*	*Frequency* *(sessions per week)*	*Total weekly repetitions*	*Intensity*	*Inter-set Rest (sec)*
2-week Familiarization Period					
Hamstring exercise	As per intervention group allocation				
Incline DB Press	2 × 10 (2:0:1)	2	40	70–75% 1RM (7 RPE)	60
Chest-supported Incline DB Row	2 × 10 (2:0:1)	2	40	70–75% 1RM (7 RPE)	60
Prone Shoulder Y-T-W	2 × 10 (2:0:1)	2	40	70–75% 1RM (7 RPE)	60
Biceps curls to Triceps pressdown	2 × 15 (2:0:1)	2	60	70–75% 1RM (7 RPE)	60
Half Ups-Half Downs Crunches	2 × 10 each (1:1:1)	2	40	Bodyweight	60
4-week Progressive Training Period					
Hamstring exercise	As per intervention group allocation				
Incline DB Press	3 × 10 (2:0:1)	2	60	70–75% 1RM (7 RPE)	60
Chest-supported Incline DB Row	3 × 10 (2:0:1)	2	60	70–75% 1RM (7 RPE)	60
Prone Shoulder Y-T-W	3 × 10 (2:0:1)	2	60	70–75% 1RM (7 RPE)	60
Biceps curls to Triceps pressdown	3 × 12 (2:0:1)	2	72	70–75% 1RM (7 RPE)	60
Half Ups-Half Downs Crunches	3 × 10 each (1:1:1)	2	60	Bodyweight	60

Abbreviations: DB = dumbbell, RM = repetition maximum, RPE = rate of perceived exertion, ECC = eccentric, ISO = isometric, CON = concentric

The hamstring-specific training will consist of the same number of repetitions performed between the RDL and the NHE. The NHE will be performed in the power rack with a pad placed under the knees and the ankles secured using the safety pins. Participants will be instructed to maintain their ankles in a dorsiflexed position, lower themselves as close to the ground as possible at a constant and controlled speed while maintaining a neutral position of the hips and trunk, and to cross their arms in front of their chest. Once an athlete reaches the ground, they will push themselves back up to the starting position while minimizing the amount of time between repetitions (< 2 s). During the familiarization period, the relative intensity will be lower compared to the 4-week progressive training to ensure each participant performs the exercise with proper technique and progressively works up to the demands of the intervention. We have observed in testing that most athletes complete the NHE in approximately 4 to 6 s [81]. This is consistent with a recent study in male field hockey players where mean (standard deviation) time to complete the NHE was 4.17 (1.14) seconds with a dorsiflexed ankle [76]. The relative intensity will be progressively increased by modifying the time to complete the NHE (from 4 to 6 s, Table 2) throughout the training period. The relative intensity during the intervention (8–9 RPE) will be maintained across the NHE by having athletes hold weight plates across their chest (as necessary). Training logs will be used to track athletes’ training loads.

The RDL will be performed in a similar manner as the 3RM testing with the barbell placed on the safety pins positioned slightly below the knee. The time to complete the eccentric portion of the RDL will be performed in a progressive manner and time-matched with the NHE (Table 2) with the athlete returning to the start position with a maximal concentric hip extension. Relative training intensity will be maintained by adding or removing resistance to the exercise. The prescribed 8–9 RPE equates to approximately 82–92% 3RM. Wrist straps will be worn during the RDL training sessions to ensure the training loads adhere to the intensity prescription and are not limited by the participant’s grip strength. The description of the interventional program is shown in Table 2. Both groups will train a total of 2 sessions per week.

**Table 2 Tab2:** Hamstring intervention program

*Training Period*	*Week*	*Frequency (sessions per week)*	*Sets x Reps*	*Target Eccentric Contraction Duration* *(sec per rep)*	*Target intensity* *(0 to 10 RPE)*	*Inter-set rest (sec)*
**Familiarization**	1	2	3 × 3	4 s through full ROM	5	90
	2	2	3 × 4	5 s through full ROM	7	90
**Intervention**	3	2	4 × 4	6 s through full ROM	≥ 8	120
	4	2	4 × 4		≥ 8	120
	5	2	4 × 4		≥ 8	120
	6	2	4 × 4		≥ 8	120

† Training prescription applied twice per week over the 6-week intervention period for both Nordic hamstring exercise (NHE) and Romanian deadlift (RDL) groups. NHE will be performed to each participant’s maximum range of motion at the prescribed eccentric tempo. RDLs will be executed at the prescribed tempo ranging between 4–6 s of eccentric lowering and returning to the start position as fast as possible. Absolute intensity progressively increased on an individual basis in both groups by adding external load to ensure target eccentric contraction duration and intensity is being met as prescribed below

Abbreviations: Rep(s) = repetition, ROM = range of motion, sec = seconds

